**Research environment**

The research environment is the Colonoscopy Department of Ayatollah Taleghani Medical Education Center.

**Research tools:**

The data collection tool in this research is as follows:

1- The demographic information questionnaire has 20 questions including the patient's age, sex, education, marital status, occupation, type of health insurance, reason for hospitalization, duration of hospitalization, history of illness, history of underlying illness, history of illness in the family (Appendix No. 1).

2- Colonoscopy satisfaction questionnaire (Appendix No. 2).

**Validity and reliability of tools**

In this research, to determine the validity of the used questionnaires, the method of determining face and content validity will be used (27, 28). The above questionnaires are a combination of different studies. Therefore, its validity and reliability will be checked. The validity check will be done by the method of form and content validity check, and in the reliability check based on the type of instrument, the Cronbach's alpha method and the test-retest will be used. In order to check face validity and qualitative content validity, the tools will be available to 10 faculty members of Shahid Beheshti University of Medical Sciences and experts and nurses with experience in the colonoscopy department, and after collecting their opinions, the necessary corrections will be made. It will be done in tools.

In the next step, content validity will be checked in a quantitative way, using the opinions of 10 members of the Faculty of Nursing and Midwifery of Shahid Beheshti University of Medical Sciences and experts and nurses with experience in colonoscopy regarding simplicity, ambiguity, the relevance of the items, the validity index of the content and the necessity of the items are calculated. The content validity index is higher than 0.7 in each case of simplicity, ambiguity, relevance in each item. The content validity coefficient based on the number of professors participating in the validity review (minimum 10 people are considered) is 0.49 acceptable according to the Lavshe table (27,28)^[[1]](#footnote-1)^. Cronbach's alpha and test-retest will be used for the reliability of the tool (27, 28).

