**data analysis method**

Analyzing the research data using statistical package software for social sciences version 20, and using descriptive tests such as mean, variance, and standard deviation, and using inferential tests such as chi-square, independent t-test, and analysis of variance, the data will be analyzed. The Smirnov Kolmograph test will be used to check the normality of the data. To compare the two groups, chi-square, Menio-Whitney and independent t-tests will be used, and to compare the results in the intervention and control groups, independent t-test or Menio-Whitney statistical tests will be used. In all tests, a significance level of less than 0.05 will be considered.

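### The content validity cut-off of 0.49 does not fit the panel of ten it is tied to, and one fixed value does not suit a panel of open size (minor)

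*Protocol*

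**What the plan says.** The protocol (Validity and reliability of tools) explains that the questionnaires are assembled from several studies and so need checking. For the quantitative step, raters judge each item, and "the validity index of the content and the necessity of the items are calculated". The raters are described as "using the opinions of 10 members of the Faculty of Nursing and Midwifery", and the same sentence adds experts and nurses with colonoscopy experience. It is unclear whether ten is the whole panel or only its faculty part.

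The cut-off is explicitly linked to panel size: "The content validity coefficient based on the number of professors participating in the validity review (minimum 10 people are considered". The same sentence gives the value and attributes it to a cited table: "minimum 10 people are considered) is 0.49 acceptable according to the Lavshe table". No significance level, sidedness, chance level or answer categories are given for the necessity rating. The only significance level is under data analysis method: "In all tests, a significance level of less than 0.05 will be considered".

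**The concern.** A cut-off for rater agreement has to be stricter in a small panel, because a few raters reach a high level of agreement by chance more easily than many do. The protocol accepts this by tying the value to the number of raters. It then attaches one number, 0.49, to a panel of ten or more. If 0.49 suits a larger panel, ten raters can pass an item on weaker evidence than the rule implies. At stake is the make-up of the satisfaction questionnaire, which supplies the dependent variable: a one-vote difference can decide whether a borderline item stays as it is or needs revision.

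**Working it through.** **Inputs.** Cut-off 0.49 and minimum panel 10 (protocol, Validity and reliability of tools). Three things are assumed because the protocol does not give them: the usual formula for the ratio, a 50% chance that an indifferent rater calls an item necessary (the level at which the ratio is zero), and 5% as the reference level.

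**Step 1: what 0.49 means with ten raters.** Ratio = (n − N/2)/(N/2), where n of N raters call the item necessary. With N = 10:
- 7 votes: (7 − 5)/5 = 0.40, below 0.49
- 8 votes: (8 − 5)/5 = 0.60, above 0.49
- 9 votes: (9 − 5)/5 = 0.80

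The working rule is therefore 8 of 10.

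**Step 2: chance probability with ten raters.** From the binomial with N = 10 and p = 0.5:
- P(8 or more) = (45 + 10 + 1)/1024 = 56/1024 = 0.0547
- P(9 or more) = (10 + 1)/1024 = 11/1024 = 0.0107

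The smallest count below 5% one-sided is 9 of 10.

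**Step 3: can 0.49 be reproduced as a 5% cut-off at N = 10?**
- Normal approximation, one-sided: 1.645/√10 = 0.52 (in practice also 8 of 10)
- Normal approximation, two-sided: 1.96/√10 = 0.62 (in practice 9 of 10)
- Exact binomial, one-sided: 0.80 (9 of 10)

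None gives 0.49. The two-sided approximation gives 1.96/√15 = 0.506 and 1.96/√16 = 0.490, so 0.49 suits about 15 to 16 raters on that method.

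**Step 4: the same cut-off at other panel sizes** (exact, one-sided, p = 0.5):

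| Raters | Votes needed under 0.49 | Chance probability |
|---|---|---|
| 10 | 8 | 0.0547 |
| 11 | 9 | 0.0327 |
| 12 | 9 | 0.0730 |
| 13 | 10 | 0.0461 |
| 14 | 11 | 0.0287 |
| 15 | 12 | 0.0176 |
| 16 | 12 | 0.0384 |

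The probability moves up and down with panel size. It exceeds 5% at 10 and at 12.

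**Step 5: sensitivity to the chance level.** If an indifferent rater chose the necessary category with probability 1/3 (for example, with three answer categories), P(8 or more of 10) = 0.0034.

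**Step 6: cost of a stricter count.** For an item that 90% of experts would truly endorse:
- P(9 or more of 10) = 0.9^10 + 10 × 0.9^9 × 0.1 = 0.736, so 26% are rejected
- P(8 or more of 10) = 0.736 + 45 × 0.9^8 × 0.1^2 = 0.930, so 7% are rejected

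**The case against.** The strongest reply is that the protocol sets no 5% rule for keeping items. Its 0.05 is written for the statistical tests, and the 50% chance level comes from this review. The shortfall, 5.47% against 5%, is small; it vanishes at a chance level of 1/3; and the one-sided normal value of 0.52 leads to the same 8 of 10 as 0.49. All of this stands, and it limits the size of the point. It does not remove the mismatch: none of the 5% methods tried yields 0.49 at the size the protocol names.

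Second, ten is a minimum, and the panel may be larger. That also stands: at 11 and at 13 to 16 raters the rule stays below 5%. But at 12 it does not, so the open panel size is a reason to fix the number, not a defence of a single value.

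Third, 0.49 is not the only screen. The same section sets a content validity index above 0.7 per item for simplicity, ambiguity and relevance, and provides for qualitative review with corrections. A reader might infer that this threshold alone decides what enters the outcome, or that about one item in 16 would enter by chance (16 × 0.0547 = 0.88). The documents do not support either. The other screens also apply, the text does not say that an item below 0.49 is dropped rather than revised, and the count of 0.88 requires every rater to be indifferent about every item.

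Finally, a reader might infer that the cited table was misread. The table is not at hand, so that cannot be judged; the point rests on the binomial alone.

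**Conclusion.** The point holds as a minor one. At the panel size to which the protocol attaches it, 0.49 acts as 8 of 10, with a one-sided chance probability of 0.0547 against 0.0107 for 9 of 10. More generally, one fixed cut-off does not suit a panel whose size is left open. The conclusion rests on the usual formula for the ratio, a 50% chance level and a 5% reference, none of which the protocol states for item selection.

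It should not be read as a threat to the trial's result. Both groups complete the same questionnaire, so the choice between 8 and 9 votes may change which items are scored but does not bias the comparison between groups.

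**What to change.** State the total number of raters, making clear whether experts and nurses are counted within the ten. Then replace 0.49 with the smallest vote count whose one-sided binomial probability at 0.5 is below 0.05 for that number: at least 9 of 10 (ratio 0.80) if the panel is ten. Alternatively, keep 0.49 and commit to a panel size that it fits, such as 15 or 16.

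The change takes one sentence and no extra patients, and is best made before the panel rates the items. The downside is real: with ten raters, items with exactly 8 votes would need revision, and good items would fail more often (about 26% against 7% at 90% true endorsement). The alternative of a larger panel avoids the 9-of-10 rule but requires more raters.

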**Data collection method**

In the present study, data will be collected by completing a questionnaire. In this way, after obtaining the code of ethics from the ethics committee and the letter of introduction from Shahid Beheshti University of Medical Sciences and Health Services, the researcher explains the goals and working methods to them through coordination with the officials of the Ayatollah Taleghani Medical Education Center and will conduct the study.

In order to collect data from the patients, first a written consent to participate in the research will be obtained from them, after explaining the objectives and the method of doing the work to participate in the research. Both groups complete the demographic questionnaire (Appendix 1) and the colonoscopy satisfaction questionnaire (Appendix No. 2) (colonoscopy) and the results are compared in the two control and intervention groups.

**data analysis method**

Analyzing the research data using statistical package software for social sciences version 20, and using descriptive tests such as mean, variance, and standard deviation, and using inferential tests such as chi-square, independent t-test, and analysis of variance, the data will be analyzed. The Smirnov Kolmograph test will be used to check the normality of the data. To compare the two groups, chi-square, Menio-Whitney and independent t-tests will be used, and to compare the results in the intervention and control groups, independent t-test or Menio-Whitney statistical tests will be used. In all tests, a significance level of less than 0.05 will be considered.

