***STUDY PROTOCOL***

**Research Method**

The current study is a semi-experimental study in which the effect of the independent variable (use of media in patient education) on the dependent variable (satisfaction of patients undergoing colonoscopy) will be investigated.

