**Sampling**

In this research, sampling will be done by available method and the participants will be selected purposefully in two control and intervention groups. The similarity of the two groups in terms of age, sex, education level, disease, background and cause of hospitalization will be statistically investigated.

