**Attachments**

***Appendix No. 1:***

***Questionnaire of demographic information***

1- Age: ............. years

2- Gender: male or female

3- Marital status: single, married, divorced, widowed

4- Education:...............

5- Occupation:............

6- Reason for admission:............

7- Hospitalization period:............

8- Type of health insurance:..............

9- Amount of income:..............

10- History of drug use: yes, no

11- History of cancer in other family members: yes, no

12- History of other underlying diseases: yes, no

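### The groups are formed by purposeful selection, but the satisfaction comparison is fixed as an unadjusted test, so imbalance in measured factors passes into the result

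*Protocol*

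**What the plan says.** Under Research Method the protocol states the design: "The current study is a semi-experimental study". Under Sampling it describes how the groups arise: "sampling will be done by available method and the participants will be selected purposefully in two control and intervention groups". No randomisation, matching or stratification is described. The Data collection method section describes only the demographic and satisfaction questionnaires, so there is no pre-intervention satisfaction score to adjust for.

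The safeguard against unlike groups is a check: "The similarity of the two groups in terms of age, sex, education level, disease, background and cause of hospitalization will be statistically investigated". The data analysis method section gives the tools: "To compare the two groups, chi-square, Menio-Whitney and independent t-tests will be used". All tests use the 0.05 level. For the outcome, the same section says "to compare the results in the intervention and control groups, independent t-test or Menio-Whitney statistical tests will be used". Analysis of variance appears once, in a general list ("using inferential tests such as chi-square, independent t-test, and analysis of variance"), with no factor or covariate named.

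**The concern.** With purposeful selection, nothing in the design makes the groups alike, even on average. A plain difference in satisfaction then mixes the effect of the educational media with any difference in age, education, reason for admission and so on that is itself related to satisfaction.

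The similarity check does not repair this. A significant result triggers nothing. A non-significant result with 37 to 50 patients per group is weak evidence of similarity, because the test has little power against imbalances large enough to matter. The variables are collected and compared, but never enter the outcome analysis. At stake is whether a significant difference in satisfaction can be read as an effect of the intervention.

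**Working it through.** **Inputs from the protocol (Adult sample size; data analysis method).** Two-sided α = 0.05 (z = 1.96), power 0.90 (z = 1.28), planned effect 0.75 SD, minimum 37 per group, 50 per group enrolled, and 0.05 for every test.

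**Inputs assumed, because the protocol gives none.** True imbalance in one covariate d = 0.3 to 0.5 SD; within-group correlation of that covariate with satisfaction ρ = 0.3 to 0.5.

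**1. The plan's own figure.** n = 2 × (1.96 + 1.28)² / 0.75² = 2 × 10.4976 / 0.5625 = 37.32. This reproduces the stated 37 (38 if rounded up), so 0.75 SD is a sound yardstick for the bias.

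**2. What the similarity test can see.** This is the power of a two-sample t-test with noncentrality d × √(n/2). For d = 0.4 and n = 50, noncentrality is 0.4 × 5 = 2.0.

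| True imbalance | Detected, 37 per group | Detected, 50 per group |
|---|---|---|
| 0.3 SD | 25% | 32% |
| 0.4 SD | 40% | 51% |
| 0.5 SD | 56% | 70% |

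An imbalance of 0.4 SD is thus missed 60% of the time with 37 per group and 49% with 50. Conversely, if the groups are truly alike, six independent tests at 0.05 give at least one false signal with probability 1 − 0.95⁶ = 0.26.

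**3. Bias of the unadjusted difference.** Bias = ρ × d, in SD of satisfaction.
- Lowest case: 0.3 × 0.3 = 0.09 SD; 0.09 / 0.75 = 12% of the planned effect.
- Middle case: 0.5 × 0.4 = 0.20 SD; 0.20 / 0.75 = 27%.
- Highest case: 0.5 × 0.5 = 0.25 SD; 0.25 / 0.75 = 33%.

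The bias can go in either direction.

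**4. False-positive rate of the unadjusted t-test when the intervention has no effect.** Noncentrality = bias × √(n/2).

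| Bias | 37 per group | 50 per group |
|---|---|---|
| 0.09 SD | 6.7% | 7.3% |
| 0.20 SD | 13.6% | 16.8% |
| 0.25 SD | 18.6% | 23.6% |

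**5. The same rate when the similarity test is non-significant (simulation).** For d = 0.4, ρ = 0.5 and 50 per group, the bias among such trials is 0.12 SD (0.12 / 0.75 = 16% of the planned effect) and the false-positive rate is about 7%. Among trials where the similarity test is significant, the rate is 26%. The parts agree with step 4: 0.49 × 7% + 0.51 × 26% ≈ 17%. Over the scenarios simulated (d = 0.4 with ρ = 0.3 or 0.5, and d = 0.5 with ρ = 0.5, at 37 and 50 per group), the rate after a non-significant test is 5.6% to 8.1%.

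**6. After adjustment for the same covariate (same simulated scenarios).** Bias is about 0 and the false-positive rate is 4.7% to 5.0%.

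**The case against.** *The larger false-positive rates are not those of undetected imbalance.* This stands. A reader might join the 49% chance of missing a 0.4 SD imbalance to the 17% false-positive rate and conclude that hidden imbalance alone causes the latter. Step 5 shows otherwise: most of the excess comes from trials in which the baseline table would show the difference. The step 4 figures are still the right ones for the plan as a whole, because the outcome test is the same whatever the similarity test shows.

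*Both drivers are assumptions.* This also stands. Nothing in the protocol supports a particular correlation between a demographic item and satisfaction, so the size must be read as a range. Factors unrelated to satisfaction cause no bias at all.

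*Adjustment would also sharpen the estimate.* A reader might infer a power gain, for example from 81.5% to about 89% with 30 per group if covariates explain 20% of the variance. That calculation divides 0.75 by √0.8, which presumes covariates balanced between groups and ignores the degrees of freedom used. Here the premise is imbalance. With five covariate parameters, a variance inflation of 1.10 gives 86.0%, and 1.25 gives 81.4%, so the gain can vanish. The case for adjustment is bias, not precision.

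*The form may lack the variables.* The Research tools section says "The demographic information questionnaire has 20 questions", while Appendix No. 1 ends at "12- History of other underlying diseases: yes, no". A reader might infer that adjustment variables are missing. The mismatch is real but separate: age, sex, education, reason for admission and underlying disease are items 1, 2, 4, 6 and 12.

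*An SAP not shown may add an adjusted model.* It may. But the protocol names the outcome tests itself, and the general mention of analysis of variance specifies no covariate. A reader might also infer that the normality test selects between t-test and Mann-Whitney. The text does not say so, and the point does not depend on it.

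**Conclusion.** The point holds. The protocol pairs non-random group formation with an unadjusted outcome test and a similarity check without consequence. Followed as written, it carries measured imbalance related to satisfaction into the result.

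The mismatch between design and analysis rests on the text alone. Its size rests on the two assumed ranges and on t-test calculations for one covariate, so it is indicative. It is enough to call for a change to the main analysis. It does not show that the result will be biased, since that depends on an imbalance nobody has yet observed. Nor would adjustment make the comparison equivalent to a randomised one.

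**What to change.** In the data analysis method section, name as the main analysis a linear model of the satisfaction score on group, adjusted for age, sex, education, underlying disease (yes/no) and reason for admission. Report the adjusted difference with its 95% confidence interval. Fix the covariates in advance, regardless of any similarity test. Education and reason for admission are blank text fields on Appendix No. 1, so define two or three categories for each before the data are seen. The model then has 3 + (1 to 2) + (1 to 2) = 5 to 7 covariate terms, for 74 (2 × 37) to 100 (2 × 50) patients.

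Keep the unadjusted t-test and Mann-Whitney test as supportive analyses. In the Sampling section, replace the similarity tests with a baseline table of standardised differences. State as a limitation that selection on unmeasured factors is not removed.

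The cost is a few sentences, the coding of two free-text items and a few degrees of freedom. No new data are needed. A gain in precision should not be promised.

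Separately, reconcile the stated number of questions with the items on Appendix No. 1; this fix does not depend on it.

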**Attachments**

***Appendix No. 1:***

***Questionnaire of demographic information***

1- Age: ............. years

2- Gender: male or female

3- Marital status: single, married, divorced, widowed

4- Education:...............

5- Occupation:............

6- Reason for admission:............

7- Hospitalization period:............

8- Type of health insurance:..............

9- Amount of income:..............

10- History of drug use: yes, no

11- History of cancer in other family members: yes, no

12- History of other underlying diseases: yes, no

***Appendix No. 2:***

***Colonoscopy satisfaction questionnaire***

**Before colonoscopy**

1) Have you been seen as an outpatient by a doctor to discuss your condition and the planned catheterization procedure?

Yes, No

2) Has the doctor explained what is done during the colonoscopy procedure?

Absolutely, To Some Extent, No

3) During the pre-op clinic visit, were you told what to do after the colonoscopy?

Absolutely, To Some Extent, No

4) Have you been given enough information before the colonoscopy procedure?

Yes, No

5) Has the doctor or nurse explained what will be done during the procedure during the visit before the colonoscopy?

Absolutely, To Some Extent, No

6) Did you have unanswered questions about the procedure before being admitted to the hospital?

Yes, No

**During colonoscopy**

7) If you were visited by a doctor in an outpatient clinic, how would you evaluate his visit?

Weak, good, not good, average, good, excellent, not usable

8) Did you have a chance to ask the remaining questions?

Yes, No

9) Did you feel ready for the operation?

Yes, No

10) Was your experience in the colonoscopy unit what you expected?

Yes, No

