**Adult sample size**

The number of samples is obtained using the following relationship in each group:

$$n\geq2\frac{\left( z_{\alpha/2}+z_{\beta} \right)^{2} \sigma^{2}}{(\mu_{1}- \mu_{2})}$$

where the probability of type 1 error:

$$\alpha=0.05 \to z_{\alpha/2}=1.96$$

Probability of type II error:

$$\beta=0.10 \to z_{\beta}=1.28$$

$$1- \beta=0.90$$

Power of observed effect size:

$$\left( \mu_{1}- \mu_{2} \right)/{\sigma=0.75}$$

${\mu_{2},\mu}_{1}$indicate the average satisfaction score of the adults.

Minimum sample required:

$$n=2\left( 1.96+1.28 \right)^{2} \left( \frac{1}{0.75} \right)^{2} =37$$

At least 37 adults in each group should be considered for the research, and considering 40% attrition, the number of samples is 50 patients in each group.

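### Items 1 and 7 of the satisfaction questionnaire record the outpatient doctor's visit, so in purposively chosen groups a prior difference in clinic care can read as a media effect

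*Protocol*

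**What the plan says.** Research Method sets out to test "the effect of the independent variable (use of media in patient education) on the dependent variable (satisfaction of patients undergoing colonoscopy"). Adult sample size bases the study on group means that "indicate the average satisfaction score of the adults", with a standardised difference of 0.75, two-sided alpha 0.05 and 90% power. The result is 37 per group, raised to 50 for attrition.

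The only satisfaction instrument is the 16-item form in Appendix No. 2. Four items look back to clinic care or to the time before admission:

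- Item 1: "Have you been seen as an outpatient by a doctor to discuss your condition" (Yes/No).
- Item 3: "During the pre-op clinic visit, were you told what to do after the colonoscopy" (three levels).
- Item 6: "Did you have unanswered questions about the procedure before being admitted to the hospital" (Yes/No).
- Item 7: "If you were visited by a doctor in an outpatient clinic, how would you evaluate his visit" (a list of rating words plus a not-applicable type of answer). It stands under During colonoscopy.

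Under Sampling, the two groups are formed by purposive selection, and their similarity is to be tested on six named characteristics. An earlier outpatient visit is not among them, nor among the questions printed in Appendix No. 1. The data analysis section compares the groups by independent t-test or Mann-Whitney test and names no covariate. The protocol gives no scoring rule and does not say when the education is delivered.

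**The concern.** Item 1 is a fact about the patient's route to the department. Item 7 judges a doctor's consultation. Neither asks about something that the media are meant to change, yet both sit in the instrument whose score is the outcome.

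In a randomised trial such items would mainly add noise. Here the groups are chosen, so they also open a direct path for bias. If one group contains more patients who came through the outpatient clinic, or whose clinic visit went better, its satisfaction score is higher before any education is given. Nothing described in the protocol would detect or remove that difference, and it would be reported as an effect of the media.

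**Working it through.** **1. The plan's own figure.** Inputs from Adult sample size: z values 1.96 and 1.28, standardised difference 0.75.

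n = 2(1.96 + 1.28)² / 0.75² = 20.995 / 0.5625 = 37.3 per group.

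The stated 37 reproduces (38 if rounded up). Normal-approximation power is Φ(0.75·√(n/2) − 1.96), which is 89.7% at 37 and 96.3% at 50 per group. These figures concern the mean satisfaction score, with no subset of items named.

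**2. Which items the education can move.**

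| Item | Asks about | Can patient media change it? |
|---|---|---|
| 1 | whether the outpatient visit happened | No, whenever the media are given |
| 7 | quality of that visit | The visit itself is not changed; the rating might be coloured |
| 3 | what was said at the pre-op clinic | Only possibly, and only if education comes by then |
| 6 | open questions before admission | Yes, if education comes before admission |

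**3. Possible weight in the score (assumed scoring).** Suppose each response step counts one point: eleven Yes/No items give 11, three three-level items give 6, item 7 with six printed rating words gives 5, and item 14 gives 4. The total is 26. Items 1 and 7 then hold (1 + 5)/26 = 23%. One rating word is printed twice in item 7. With five distinct words the share is (1 + 4)/25 = 20%. Under equal weighting it is 2/16 = 12.5%.

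**4. Bias from a prior difference.** If unvisited patients score zero on both items, a difference Δp in the proportion visited shifts the mean total by Δp × (1 + mean item 7 rating among the visited) points. The protocol gives neither Δp nor the SD of the score, so the shift b in SD units has to be assumed. With no true effect, the chance of P < 0.05 is Φ(b/s − 1.96) + Φ(−b/s − 1.96), where s = √(2/n):

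| b (assumed) | 37 per group | 50 per group |
|---|---|---|
| 0.1 SD | 7% | 8% |
| 0.2 SD | 14% | 17% |
| 0.3 SD | 25% | 32% |

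This calculation does not depend on how the 0.75 SD is read.

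**5. Dilution, only if the 0.75 SD belongs to the responsive items.** Assume 16 equally weighted items with equal variance and common correlation ρ, of which m respond. The effect on the total is 0.75 × √[(m + m(m−1)ρ)/(16 + 240ρ)].

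- Items 1 and 7 inert (m = 14). For ρ = 0: 0.75 × √(14/16) = 0.70. For ρ = 0.5: 0.75 × √(105/136) = 0.66. Power is 86% to 81% at 37 and 94% to 91% at 50 per group; n for 90% power is 43 to 49.
- Items 3 and 6 also inert (m = 12). The effect is 0.65 to 0.57 SD, power at 37 is 80% to 69%, and n for 90% power is 50 to 66.
- Raw point sum with items 1 and 7 inert (simulation, ρ 0.1 to 0.5, equally likely response categories). The effect is about 0.59 to 0.60 SD, with power 71% to 72% at 37 and 83% to 85% at 50.

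If the 0.75 SD already refers to the whole score, none of this loss occurs.

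**The case against.** A reader might infer that all four items are fixed before the education starts, because "The research environment is the Colonoscopy Department" and "first a written consent to participate in the research will be obtained from them". The protocol does not support that. The first statement names a setting. The second puts consent before data collection. Neither says when or where the media are delivered, and the inclusion criterion on access to virtual space and videos is compatible with remote delivery before admission. In that case item 6 is a legitimate target of the education and item 3 may respond too. This objection stands for items 3 and 6. It does not rescue item 1, and it helps item 7 only as far as the education colours the memory of the doctor's visit.

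A reader might also infer that the trial has lost its stated power. That requires moving the 0.75 SD from the average satisfaction score to a subset of items, which the sample-size section does not do. Any dilution may already be inside the 0.75.

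Three further objections carry some weight:

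- Scoring may be fixed in an analysis plan that is not shown, so entry of items 1 and 7 into the score is inferred from the form. This is a reason to state the exclusion. It does not show that the items are excluded.
- The expert review of relevance and necessity under Validity and reliability of tools may remove these items. Nothing ensures that it will.
- The confounding comes from purposive selection, and these items are only one route for it. That is correct, but this route leads straight into the outcome and can be closed.

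**Conclusion.** The point holds for items 1 and 7. They describe an outpatient visit that the media neither create nor form part of, and the form offers no ground for leaving them out of the score. With purposive groups, no check on prior clinic care and no named adjustment, a difference in that care would count as a media effect. For items 3 and 6 the point is conditional on an education time that the protocol does not state.

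The size of the bias cannot be derived from the protocol. The false-positive rates of 7% to 32% above illustrate assumed shifts of 0.1 to 0.3 SD and are not estimates for this trial. The 20% to 23% share rests on an assumed raw point sum. Reduced power is a possibility only under a reading of the 0.75 SD that the text does not give.

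**What to change.** - State when the education is given relative to the outpatient visit, the pre-op clinic visit and admission.
- Leave items 1 and 7 out of the satisfaction score, and also items 3 and 6 if the education comes after the time they ask about. Report the excluded items separately by group.
- Add the prior outpatient visit (item 1) to the similarity check under Sampling, and adjust the group comparison for it, for example by a linear model with group and visit as terms. Item 7 is undefined for patients without a visit, so it is better described than used as a covariate.
- State in Adult sample size that the 0.75 SD refers to the resulting score.

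The cost is small. Item 1 asks about a past event and is already on the form, so no new question, no additional measurement time and no more patients are needed. The score becomes slightly shorter (14 items, or 12 if items 3 and 6 also leave) and no longer matches the source questionnaires item for item. Adjustment for the visit deals with that one route and does not remove other confounding from purposive selection.
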